**Methods:**

DAN-APNO is a cross-sectional study at the Department of Cardiology, Herlev-Gentofte Hospital recruiting patients with AF referred to anticoagulation initiation aged 18 to 90 years without known sleep apnea. At least 150 patients will be recruited and undergo medical history, clinical evaluation, several sleep-apnea questionnaires, and a sleep-recording evaluation for four nights with sleep apnea home-monitoring device NightOwl™. Additionally, the first 20 participants and participants with moderate-severe sleep apnea by screening are referred to cardio-respiratory monitoring (CRM). This clinical evaluation allows the comparison of standard evaluation method and the NightOwl™. Clinical measures include Apnea–Hypopnea Index (AHI), Oxygen Desaturation Index (ODI), pulse rate, as well as questionaries about sleep apnea assessment and the clinical feasibility of the NightOwl™ device. Main outcomes comprise analysis of the prevalence and severity of sleep apnea, and clinical and demographic predictors of moderate and severe sleep apnea. In addition, correlation analyses for accuracy measures between CRM and NightOwl™ will be conducted along with patient ease-of-use and satisfaction questionnaires.

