### Outcomes

The primary outcome of the study is the prevalence with 95% confidence intervals of sleep apnea in patients with AF detected by NightOwl™. This analysis will be total and stratified by severity of sleep apnea.

The secondary outcome will be an exploratory analysis of predictors of sleep apnea and predictors of moderate and severe sleep apnea in the participants using baseline characteristics and clinical data of the participants.

Other outcomes of interest are;The correlation between NightOwl™ and CRM diagnostic testing for sleep apnea and the correlation between sleep apnea screening questionnaire for CRM and NightOwl™.Evaluation of user-experience and compliance with NightOwl™.The evaluation of user-experience and compliance will consist of a survey questionnaire build with help from CATCHET Unified Method for Assessment of Clinical Feasibility (CUMACF) [21]. The purpose of this method is to deliver a standardized way of measuring clinical feasibility of the many new technologies being designed and tested. The clinical feasibility questionnaire is divided into three parts: Usage Adoption, Perceived Usefulness and Usability, and Health Efficacy.Inter-variability of NightOwl™ recordings.Recordings of four nights will be used to assess any inter-variability between the NightOwl™ recording. Furthermore, the four nights recording can clarify potential night-to-night fluctuations and thereby gives a more precise screening of the presence of sleep apnea.

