**Fig. 3 Fig3:**
[figure not shown]
NightOwl™ Data Output (sample). The NightOwl™ derives all parameters sufficient to diagnose sleep apnea

The product complies with Medical Device Directive 93/42/ECC and amendments 2007/47/EC requirements. The product is CE marked i.e. the product is authorized for clinical use. Instructions of use and complete product description can be found at http://www.ectosense.com/eifu.

Data captured from NightOwl™ comprises data from four sleep evaluations and consists of the parameters AHI, ODI, heart rate and sleep time. The AHI is graded into four different classifications, them being without sleep apnea (AHI < 5), mild sleep apnea (5 < 15), moderate sleep apnea (15 < 30) and severe sleep apnea (> 30). Thus, NightOwl™ defines sleep apnea as AHI > 5. The data captured from the four nights is to be presented in average quantities thereby counteracting potentially variations in the participants’ sleep data from night to night.

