### Cardiorespiratory monitoring

The CRM for the 20 first participants and for the participants where the home test is showing AHI > 15 (moderate-to-severe sleep apnea) is provided by the Department of Pulmonology, Herlev-Gentofte University Hospital and will quantify the frequency, duration and type of each sleep apnea event (obstructive or central) by measuring AHI, ODI, oximetry distribution and heart rate. Potential treatment for sleep apnea will be at the discretion of the attending sleep apnea physician. Simultaneously with undergoing the CRM, the participants will also be assessed by the NightOwl™ the same night. This simultaneity in the recording by the two different monitoring-methods allows for a direct analysis of the correlation of AHI (and other parameters) measured by CRM and NightOwl™.

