### Statistical analysis

The prevalence will be calculated by the proportion of participants with sleep apnea out of all participating individuals. The differences between patients with and without a diagnosis of sleep apnea (i.e. AHI > 5) will be assessed by the independent sample t test for continuous variables and the χ2 test for categorical variables. For the participants undergoing CRM, accuracy measurements of the home-monitoring of the NightOwl™ will be conducted by correlation analyses including scatter plots based on AHI measured by CRM versus AHI measured by NightOwl™ and receiver operator characteristics (ROC) with area under the curve (AUC) values.

As an exploratory analysis, a multivariate logistic regression analysis will be performed to test the predictors of a set of factors to detect the presence of any sleep apnea and presence of severe sleep apnea. These include age, body mass index (BMI), sex, neck circumference, European Heart Rhythm Association (EHRA) score (0–4), type of AF (new AF, paroxysmal, persistent AF, permanent AF), prior treatment for AF, blood samples, echocardiographic data and electrocardiogram data. Similar analysis using a multivariate logistic regression will evaluate if commonly used sleep apnea questionnaire can predict presence of sleep apnea in these patients. Correlation analyses will also be conducted of the clinical feasibility questionnaires.

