### Power calculations

Assuming a prevalence of severe sleep apnea of 10% in the population compared to 4% in the general population, with alpha 0.05 and a power of 80% a sample size of 113 was calculated. We plan to include 150 patients due to drop-outs, and potentially difficulties of patients applying the device.

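### The moderate-or-severe part of the secondary predictor outcome has no matching model: Statistical analysis models any and severe sleep apnea instead

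*Protocol article*

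**What the plan says.** Three places in the protocol article describe the predictor analysis.

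- **Abstract, Methods.** The main outcomes include "clinical and demographic predictors of moderate and severe sleep apnea". Predictors of any sleep apnea are not mentioned there.
- **Outcomes.** The secondary outcome has two parts: "predictors of sleep apnea and predictors of moderate and severe sleep apnea in the participants using baseline characteristics".
- **Statistical analysis.** A multivariable logistic regression, labelled exploratory, is to be fitted "to detect the presence of any sleep apnea and presence of severe sleep apnea".

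The severity classes are set under The device (text after Fig. 3): "moderate sleep apnea (15 < 30) and severe sleep apnea (> 30". Under Cardiorespiratory monitoring, the combined group is identified where "the home test is showing AHI > 15 (moderate-to-severe sleep apnea"; Study design uses the same AHI > 15 criterion.

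Power calculations uses severe disease: "Assuming a prevalence of severe sleep apnea of 10% in the population compared to 4% in the general population", and "with alpha 0.05 and a power of 80% a sample size of 113 was calculated". Planned enrolment is 150.

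**The concern.** The outcome definition and the analysis text name different dependent variables. AHI above 30 is a subset of AHI from 15 upward, so a model for severe disease answers a narrower question than the one declared. If the Statistical analysis section is followed as written, the predictor question that the abstract advertises is never addressed.

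Two things are at stake. First, with two versions on record, either could later be reported as the planned one. Second, the outcome that is modelled is the rarer of the two, and the list of candidate predictors is long.

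**Working it through.** **1. Which planned analyses use the AHI 15 boundary?**

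| Planned analysis (Statistical analysis) | Outcome or split |
|---|---|
| t tests and chi-squared tests | AHI > 5 against the rest |
| Logistic model 1 | any sleep apnea |
| Logistic model 2 | severe sleep apnea |
| Questionnaire logistic model | presence of sleep apnea |
| Correlation and ROC | NightOwl against CRM; not a predictor analysis |

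None is specified at AHI 15. If moderate and severe are read as two separate outcomes instead of one combined group, the gap remains, because moderate disease then has no model.

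**2. The plan's own sample size.** Inputs from Power calculations: p0 = 0.04, p1 = 0.10, alpha 0.05 (sidedness not stated), power 80%. A two-sided one-sample test of a proportion gives

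n = [1.960 × √(0.04 × 0.96) + 0.842 × √(0.10 × 0.90)]² / (0.10 − 0.04)² = 112.56, rounded up to 113.

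This reproduces the stated figure. It sizes a comparison of prevalence with a fixed rate, not a regression.

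**3. Cases in the severe model** (N × prevalence):

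| Severe rate | Source | N = 113 | N = 150 |
|---|---|---|---|
| 10% | Power calculations | 11.3 | 15.0 |
| 11.2% | Background, non-cardiac surgery study | 12.7 | 16.8 |
| 28% | Background, AF study (n = 100) | 31.6 | 42.0 |

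**4. Candidate parameters.** Age 1, BMI 1, sex 1, neck circumference 1, type of AF 3 (four levels), prior treatment 1, EHRA score 1 if linear, and blood samples, echocardiographic data and electrocardiogram data counted as only 1 each: 1 + 1 + 1 + 1 + 3 + 1 + 1 + 3 = 12. With EHRA categorical (0–4, so 4 parameters) the count is 15. The last three blocks will probably contribute more, so 12 is a minimum.

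Cases per parameter for the severe model:
- at 10%: 11.3/15 = 0.75 to 15.0/12 = 1.25;
- at 28%: 31.6/15 = 2.1 to 42.0/12 = 3.5.

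**5. The moderate-or-severe outcome.** The article gives no prevalence. As an assumed range, 20% gives 23 to 30 cases, 30% gives 34 to 45, and 40% gives 45 to 60 (N = 113 to 150). That is 22.6/15 = 1.5 to 60/12 = 5.0 cases per parameter.

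**6. Precision, conditional on assumed rates.** For a balanced binary predictor, taking the same odds ratio at both cut-offs, the standard error of the log odds ratio scales roughly as 1/√[N p(1 − p)].
- Severe 10%, moderate-or-severe assumed 30%: √(0.09/0.21) = 0.65, about 35% smaller.
- Severe 28%, moderate-or-severe at 50%, where p(1 − p) is largest: √(0.2016/0.25) = 0.90, about 10% smaller.

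**The case against.** The strongest defence is that this is a wording mismatch in an analysis labelled exploratory in both Outcomes and Statistical analysis. The primary outcome, prevalence overall and by severity, is untouched. That stands and limits the consequence, but it does not supply the missing model.

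Several stronger readings are tempting, and the article does not support them.

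- **That the secondary outcome is not analysed, or that only severe disease is modelled.** A model for any sleep apnea is planned and covers the first part of the outcome. The severe subset of the second part is modelled too.
- **That the severe model will have 11 to 15 cases.** This holds only at the 10% planning rate. The AF study cited in the Background points to about 32 to 42, so the article does not show that a severe regression is impossible.
- **That the wider outcome cuts the standard error by about a third.** This rests on an assumed 30% prevalence and equal odds ratios at both cut-offs. With 28% severe, the same formula allows at most about 10%.
- **That the cut-off can be chosen freely afterwards.** The severity classes are fixed under The device. What is open is which named class is modelled.

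It can also be said that changing the outcome does not cure sparse data. That is correct: even 60 cases is only 5 per parameter at the minimum count, and the length of the predictor list drives this.

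Finally, one might argue that severe disease was intended because the study was sized on it. The sizing concerns prevalence, and neither Outcomes nor the abstract singles out severe disease for the predictor question.

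**Conclusion.** The point holds as an inconsistency inside the article. The abstract and Outcomes name moderate and severe sleep apnea, Statistical analysis models any and severe, and nothing else reconciles them. This is not a detail left to a fuller document, since the article states two different dependent variables.

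The gap is one of the two parts of the secondary outcome. The severe model that stands in its place would have about 11 to 15 cases at the 10% planning rate, or about 32 to 42 at the cited 28%, against at least 12 parameters on a deliberately low count. The wider outcome contains every severe case and so cannot have fewer; how much precision that buys cannot be settled from the article. The correction is worth making, but its weight is modest because the analysis is exploratory.

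**What to change.** In Statistical analysis, make the outcome of the second logistic model moderate-or-severe sleep apnea, to match Outcomes and the abstract. Those two places give no AHI cut-off, so state it there, using the AHI 15 boundary found in Study design, The device and Cardiorespiratory monitoring. Say how a value of exactly 15 is classed for the analysis, since The device appears to start the moderate class at 15 while the other two sections write AHI > 15.

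If a severe-only model is kept, label it as additional and state that it is limited by its case count. An ordinal model across the four classes is an option, not a requirement, and it would add the assumption of a common effect across cut-offs.

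The cost is one changed or added exploratory model and a few lines of text. No new data are needed. If the severe model is replaced, the study gives up a separate regression for severe disease.

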To determine presence of sleep apnea patients with AF is therefore clinically important but is often overlooked and the diagnostic work-up is cumbersome, time-consuming and not widely available. The gold standard of sleep apnea diagnosis and AHI classification is a polysomnography (PSG) but sleep apnea is routinely diagnosed with cardiorespiratory monitoring (CRM) [14]. Academical societies have in recent decades advocated that OSA is underreported and unrecognized, and increasing evidence is supporting this statement. In a recent investigation of 1364 patients without OSA undergoing non-cardiac surgery, researchers found a prevalence of 67.6% with 11.2% suffering from severe OSA [15]. Another study of patients with AF (n = 41) the prevalence of OSA was 56% [16], and in similar study of patients with AF (n = 100), 85% had OSA (AHI ≥ 5) and severe OSA was detected in 28% [17].

A common and important clinical consequence of sleep apnea is excessive daytime sleepiness, and this clinical consequence is advocated by the use of questionnaires to assess daytime sleepiness. However, studies have shown most patients with AF report low daytime sleepiness although subsequently polysomnography analysis graded by AHI found sleep apnea present [18]. As such, screening and management of sleep apnea in patients with AF requires new prediction and assessment tools. Possibly, emerging new technologies consisting of miniaturized easily available monitoring devices and accurate algorithm development may help in the evaluation of sleep apnea status in the large number of patients with AF [19]. One of such devices is the NightOwl™, a self-applied home-monitoring device made to detect sleep apnea. It has been validated against PSG in a single-night in-laboratory setting showing promising results but a multi-night assessment of NightOwl™ in a home environment is still to be examined [20]. Potentially, the device could be an easy and inexpensive method to find undiagnosed sleep apnea in patients with AF.

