### **Hypothesis**

In patients with AF, the prevalence of unrecognized OSA is high (around 50%) and home-monitoring test using NightOwl™ is a viable, easy, and accurate test of measuring sleep apnea.

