## Discussion

This study will estimate the prevalence of unrecognized sleep apnea in patients with AF referred for anticoagulation. Furthermore, we aim to test whether a miniaturized simple home-monitoring device for detecting sleep apnea potentially can evaluate sleep apnea more conveniently and easier. Currently, patients with AF rarely undergo sleep evaluation due to limited resources, lack of standardized evaluation, lack of efficient screening tools, and cumbersome diagnostics. By making it easy and available to evaluate sleep apnea patients with AF, the prevalence of sleep apnea can be determined. Additionally, there is need for better prediction tools and risk scores to identify patients with AF and sleep apnea, by gathering extensive baseline characteristics and clinical data, we hope to be able to identify important predictors for sleep apnea in this population and can evaluate the usefulness of implemented questionnaires in this population when screening and evaluating symptom burden for sleep apnea. In addition, using such a device as the NightOwl™, patients can potentially be more independent of nurse or physician involvement to perform data collection, and clinical assessment and dialogue with patients can be prioritized.

Such cross-sectional studies do not come without limitations. Bias sample selection could apply; only patients with AF from anticoagulation clinic is asked to participate, which could limit the generalizability of our results. We do not assess prevalence of sleep apnea by gold standard of PSG but by CRM, therefore there may be higher risk of false negative and false positives. Using a smart-device such as NightOwl™ also have limitations as the device does not distinguish between central- and obstructive sleep apnea. However, the CRM validation can estimate the prevalence of central- and obstructive sleep apnea in those patients. Additionally, patients can potentially have a high amount of unrecorded data not being able to correctly determine if sleep apnea is present. The four nights of recording should limit this bias. For our secondary outcome of predictors of sleep apnea, we cannot infer causality or temporality since all data is observational and collected at first visit.

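### The exploratory predictor models list at least 12 parameters against about 11–15 severe and 56–75 any-apnea cases, too few to fit the full list jointly

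*Protocol article*

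**What the plan says.** The Statistical analysis section of the protocol article announces, as an exploratory analysis, a multivariable logistic regression for two binary outcomes: any sleep apnea and severe sleep apnea. The named factors are age, BMI, sex, neck circumference, EHRA score (0–4), AF type in four categories, and "prior treatment for AF, blood samples, echocardiographic data and electrocardiogram data".

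The sample size was not set for these models. Power calculations rests it on one prevalence comparison: "Assuming a prevalence of severe sleep apnea of 10% in the population compared to 4% in the general population", and "with alpha 0.05 and a power of 80% a sample size of 113 was calculated". Enrolment is then raised: "We plan to include 150 patients due to drop-outs, and potentially difficulties of patients applying the device". The Hypothesis section expects about half of the patients to have unrecognised apnea.

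The sections differ on the status of the predictor analysis and on its outcome. Outcomes calls it secondary and exploratory, and names moderate and severe apnea. Statistical analysis models severe apnea only. The abstract places predictors of moderate and severe apnea among the main outcomes. The Discussion says "there is need for better prediction tools and risk scores to identify patients with AF and sleep apnea" and hopes to identify important predictors. The Conclusion expects the results to inform guidelines on predictors.

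**The concern.** A logistic model's capacity is set by the smaller outcome class, not by the number of patients. With about one case per parameter, coefficients are inflated away from zero and confidence intervals are very wide. Some estimates may not exist, because a category contains no cases. At about five per parameter the fit usually converges but is still clearly optimistic.

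At stake is which characteristics get reported as predictors of apnea in AF, and how strong they appear. The Discussion's limitation on this outcome covers causality and temporality. It does not mention overfitting, so a reader of the results would have no warning of it.

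**Working it through.** **1. The plan's own sample size.** One-sample test of a proportion, two-sided alpha 0.05, power 80%, p0 = 0.04, p1 = 0.10:

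n = [1.960·√(0.04·0.96) + 0.842·√(0.10·0.90)]² / 0.06² = 112.6, rounded up to 113. The stated figure reproduces. It serves the prevalence comparison only.

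**2. Parameter count if the list is entered jointly.** Age, BMI, sex and neck circumference 4; EHRA as a linear score 1; AF type 3; prior treatment 1; blood, echo and ECG one each 3. Total 12. With EHRA categorical, 15.

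**3. Smaller outcome class per parameter (12 parameters).**

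| Outcome and prevalence | Source | Smaller class, N = 113 to 150 | Per parameter |
|---|---|---|---|
| Severe, 10% | Power calculations | 11.3 to 15 cases | 0.94 to 1.25 |
| Any, 50% | Hypothesis | 56.5 to 75 cases | 4.7 to 6.3 |
| Severe, 28% | AF study of 100 patients, Background | 31.6 to 42 cases | 2.6 to 3.5 |
| Any, 85% | same study | 17.0 to 22.5 non-cases | 1.4 to 1.9 |

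The smaller class of 150 patients cannot exceed 75, so 12 parameters never get more than 75/12 = 6.25 each, at any prevalence or AHI cut-off. That covers the combined moderate-and-severe outcome, for which the document gives no prevalence.

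**4. Expected shrinkage.** Solve N = P / [(S − 1)·ln(1 − R²/S)] for S, with P = 12 and R² = Nagelkerke R² × its maximum (0.478 at 10% prevalence, 0.75 at 50%). Nagelkerke R² of 0.15 to 0.30 is my assumption.

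- Severe, 10%: S = 0.43 to 0.61 (N = 113), 0.49 to 0.67 (N = 150).
- Any, 50%: S = 0.54 to 0.72 (N = 113), 0.61 to 0.77 (N = 150).

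The customary target is 0.9. It would need about 690 to 1,450 patients for severe and 420 to 900 for any apnea.

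**5. Simulation with 12 null parameters, maximum likelihood.** Unstable or separated fits for severe apnea at 10% were about 21% (N = 113) and 10% (N = 150). This rate depends on how the terms are coded. A rerun gave similar rates with seven continuous terms, two evenly split binary terms and four equal AF-type groups. It gave under 1% with 12 continuous terms. With AF-type shares of 30/40/20/10% and binary shares of 40% (sex) and 30% (prior treatment), it gave about 43% and 27%. The actual AF-type mix is not in the document.

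The chance of at least one falsely significant term was about 42–47% per model, with per-coefficient error near 5%. This is mostly multiplicity: 1 − 0.95¹² = 46%.

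**6. The counts may be optimistic.** Participants takes blood results as the latest available, and ECG and echo from earlier procedures in the record. Missing data considers imputation only for the primary outcome model. Complete-case fitting would leave fewer cases.

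**The case against.** The strongest reply is that the analysis is labelled exploratory in both Outcomes and Statistical analysis, and that the article is condensed. The list may be a candidate pool, with the variables, selection, estimator and validation fixed in an analysis plan not shown.

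Much of this stands:

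- The label lowers the stakes, and the prevalence estimate does not depend on these models.
- Not itemising the blood, echo and ECG variables is no fault in an article. The count of 12 takes each block once and does not rely on their contents.
- The text does not say that all factors enter one model, so the finding is conditional on joint entry.

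What the reply does not remove is that the list, followed as written, exceeds what 150 patients can support at any prevalence. The abstract and Conclusion also give the predictors more weight than an exploratory label allows.

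A reader might infer stronger points that the document does not support:

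- **That ordinary maximum likelihood is prescribed.** No estimator is named; it is only the default reading.
- **That noise will be presented as predictors.** The 42–47% risk assumes every term is null. The Background itself gives OSA in up to 17% of men and 10% of women, so sex is unlikely to be null.
- **That an inflated AUC will be published for these models.** ROC analysis is planned only for the device against CRM, and no risk score is specified.

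**Conclusion.** The point holds in a limited form. If the listed factors enter jointly, the severe-apnea model has about one case per parameter and cannot give usable adjusted estimates. The any-apnea model has about five to six and would be materially overfitted. Under the Background's figures severe apnea improves to 2.6–3.5 per parameter and any apnea falls to 1.4–1.9, so neither model becomes adequate.

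The case counts rest on the protocol's planning prevalences and on 113 to 150 evaluable patients. The shrinkage figures rest on an assumed R². The separation rate rests on the assumed spread of the categorical predictors and is the least certain number here. The parameter count and the 6.25 ceiling rest only on joint entry, one variable per block and 150 patients.

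This is worth correcting before the analysis is run. It does not threaten the primary outcome.

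**What to change.** **Any apnea.** Pre-specify a core model of about 5–7 parameters from data already collected. Age, sex, BMI, neck circumference and AF type make 4 + 3 = 7, or 56.5/7 = 8.1 to 75/7 = 10.7 cases per parameter at 50% prevalence. Fit it with Firth or ridge penalisation, and give a bootstrap optimism correction for any discrimination or calibration reported. If prevalence is nearer 85%, the non-cases become the limit (17.0/7 = 2.4 to 22.5/7 = 3.2), so the model should be cut further by a rule set in advance on the smaller class.

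**Severe apnea.** The same seven parameters would leave only 11.3/7 = 1.6 to 15/7 = 2.1 cases each. Limit this model to one or two pre-specified parameters with Firth estimation, or report univariable associations only.

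**Outcome definition.** Reconcile Outcomes (moderate and severe) with Statistical analysis (severe). The combined outcome would have more cases than severe alone.

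**Other variables and wording.** Describe blood, echo and ECG variables univariably; for any apnea the planned t and χ² tests already do this. Label the predictor results hypothesis-generating, including in the abstract and Conclusion.

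**Cost.** Analysis wording and standard software, with no new data or patients. The price is that fewer mutually adjusted associations are reported.

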## Strengths and limitations of this study

This study aims to test whether a miniaturized simple home-monitoring device for detecting sleep apnea in patients with atrial fibrillation potentially can evaluate sleep apnea more conveniently and easier.It will simultaneously gather extensive clinical characteristics, hoping to be able to identify important predictors for sleep apnea in patients with atrial fibrillation and evaluate the usefulness of implemented questionnaires when screening and evaluating symptom burden for sleep apnea.This study is limited by selection bias; only patients with atrial fibrillation from anticoagulation clinic is asked to participate, which could limit the generalizability of our results.This study does not assess the prevalence of sleep apnea by gold standard of polysomnography (PSG) but by home-monitoring device and CRM, therefore there may be higher risk of false negative and false positives.

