### Participants

Participants with AF, without known sleep apnea, and indication for anticoagulation will be recruited from the Thrombosis unit. Inclusion and exclusion criteria are shown in Box 1. The following information will be obtained from the participants:Clinical data captured at first visit: age, sex, body mass index, neck circumference and blood pressure.Data captured from electronic health system: latest available blood samples, prior health conditions (comorbidities), prior procedures performed such as electrocardiography and echocardiogram, and prior procedures related to AF such as electrical cardioversion and ablation.Questionnaires for sleep apnea screening and symptomatic burden of sleep apnea: STOP-BANG, Berlin Questionnaire and Epworth Sleepiness Scale (ESS).

**Box 1 Tab1:** Inclusion and exclusion criteria

Inclusion criteria	Exclusion criteria
Diagnosis of AF of any type	Known sleep apnea
Age < 90 years	Secondary AF
Age > 18 years	Professional drivers
	Severe heart failure (NYHA class III or IV)
	Severe chronic obstructive pulmonary disease

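### The analyses named for the screening questionnaires measure association with sleep apnea and do not report how well the questionnaires screen

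*Protocol article*

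**What the plan says.** **The aim.** In the protocol article, Strengths and limitations says the study hopes to "evaluate the usefulness of implemented questionnaires when screening and evaluating symptom burden for sleep apnea". The Discussion repeats the hope that the study "can evaluate the usefulness of implemented questionnaires in this population when screening and evaluating symptom burden for sleep apnea". Participants lists the three instruments: STOP-BANG, the Berlin Questionnaire and the Epworth Sleepiness Scale (ESS).

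**The analyses named for them.**
- Statistical analysis: "Similar analysis using a multivariate logistic regression will evaluate if commonly used sleep apnea questionnaire can predict presence of sleep apnea in these patients".
- Outcomes, among the other outcomes of interest: "the correlation between sleep apnea screening questionnaire for CRM and NightOwl™".
- Statistical analysis has one further correlation sentence, "Correlation analyses will also be conducted of the clinical feasibility questionnaires". It concerns the feasibility survey and not the three screening instruments.

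**Where accuracy is named.** For participants undergoing CRM, "accuracy measurements of the home-monitoring of the NightOwl™ will be conducted by correlation analyses including scatter plots", and the same sentence adds ROC curves with AUC values. That sentence covers NightOwl against CRM only. No sensitivity, specificity, predictive value, cut-off or AUC is named for any of the three questionnaires.

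**The concern.** Whether a questionnaire is useful for screening depends on how many people with sleep apnea it misses and how many without it are flagged. A logistic regression coefficient or a correlation shows that score and disease go together. It does not give either of those shares.

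This is more than missing detail. The article fixes a method for the questionnaires, and in the same section it assigns accuracy statistics to the device alone. What is at stake is the reading of the result. If the regression shows a clear association, a questionnaire with weak discrimination could be taken as supported for screening in this population.

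**Working it through.** **Inputs from the protocol article**
- Planned size 150, calculated size 113 (Power calculations).
- Expected prevalence of sleep apnea about 50% (Hypothesis). One cited series of 100 patients with AF had 85% (Background).
- Sleep apnea defined by AHI above 5, moderate from 15, with the four nights averaged (The device).
- CRM for the first 20 participants and those with a home-test AHI above 15 (Cardiorespiratory monitoring).

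The plan gives no figure for questionnaire performance, so there is none to reproduce. The 113 belongs to a different question, severe sleep apnea at 10% against 4%. It reproduces as a two-sided one-sample test with the normal approximation: [(1.96·√(0.04·0.96) + 0.842·√(0.10·0.90)) / 0.06]² = 112.6, rounded up to 113. It serves below only as a lower number of evaluable participants.

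**Assumption for illustration.** A questionnaire dichotomised at some cut-off, with an unadjusted odds ratio of 3.

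**Step 1: does the odds ratio fix screening performance?** For a binary test OR = [Se/(1−Se)] × [Sp/(1−Sp)]. For a chosen Se, the odds of Sp are therefore 3 ÷ [Se/(1−Se)]. The AUC of a binary test is (Se+Sp)/2. At 50% prevalence NPV = Sp/(Sp+1−Se). The counts take 75 cases and 75 non-cases.

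| Sensitivity | Specificity | AUC | NPV | Cases missed of 75 | Non-cases flagged of 75 |
|---|---|---|---|---|---|
| 0.50 | 0.75 | 0.625 | 0.60 | about 38 | about 19 |
| 0.634 | 0.634 | 0.634 | 0.634 | about 27 | about 27 |
| 0.75 | 0.50 | 0.625 | 0.667 | about 19 | about 38 |
| 0.80 | 0.429 | 0.614 | 0.682 | 15 | about 43 |
| 0.95 | 0.136 | 0.543 | 0.732 | about 4 | about 65 |

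Every row has the same odds ratio. As screens the rows differ widely.

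**Step 2: would such a questionnaire be statistically significant?** Take Se 0.75 and Sp 0.50, with expected cells 56.25, 18.75, 37.5 and 37.5.
- SE(log OR) = √(1/56.25 + 1/18.75 + 1/37.5 + 1/37.5) = 0.35
- z = ln 3 / 0.35 = 1.10 / 0.35 ≈ 3.1, p ≈ 0.002

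For Se = Sp = 0.634, the test compares 0.634 positive among cases with 0.366 among non-cases, 75 per group:
- Power = Φ{[0.268·√75 − 1.96·√(2·0.5·0.5)] / √(2·0.634·0.366)} = Φ(1.37) ≈ 0.915
- With 113 evaluable, power is about 0.82.
- With 150 and 85% prevalence (128 cases, 22 non-cases), power is about 0.66.

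**Step 3: can the planned data support accuracy measures?** Wilson 95% CIs, for an assumed sensitivity of 0.80 and specificity of 0.60:

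| Evaluable, prevalence | Cases / non-cases | CI, sensitivity 0.80 | CI, specificity 0.60 |
|---|---|---|---|
| 150, 50% | 75 / 75 | 0.70 to 0.88 | 0.49 to 0.70 |
| 113, 50% | 56 / 57 | 0.68 to 0.88 | 0.47 to 0.72 |
| 150, 85% | 128 / 22 | 0.72 to 0.86 | 0.40 to 0.78 |

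Precision is moderate near 50% prevalence. Specificity becomes imprecise if prevalence is much higher.

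**The case against.** The strongest reply is that this is an exploratory matter in a condensed article. Questionnaire performance is not among the Objectives, and it is neither the primary nor the secondary outcome. Usefulness is phrased as a hope and covers symptom burden as well as screening. A fuller analysis plan may name accuracy measures. The article also uses the word correlation loosely: for NightOwl against CRM it sits over an analysis that includes ROC, so it might cover ROC for the questionnaires too. No decision rule based on an odds ratio or a p-value is stated. These points limit the weight of the matter. They do not remove it, because the method actually named for the questionnaires is an association model, and accuracy statistics are attached only to the device.

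Three stronger readings are tempting, and the documents do not support them.
- A reader might infer that the screening question cannot be answered. It can. Questionnaires and NightOwl recordings are planned for all participants. A logistic model yields predicted probabilities and hence an AUC. If questionnaire risk category is among the variables in the planned χ2 comparisons, the 2×2 table already exists. The gap is in the analysis text, not in the design.
- A reader might infer that each questionnaire will be estimated conditional on the others or on the clinical predictors. The article does not say which terms share a model, so this is possible but not established. The working above uses one unadjusted test and does not depend on it.
- A reader might take the Background remark on low reported sleepiness in AF as evidence that all three instruments have poor sensitivity. It concerns sleepiness, which bears on the ESS, and says nothing about STOP-BANG or Berlin.

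**Conclusion.** The point stands as a mismatch between a stated purpose and the named analyses. Logistic regression and correlation can show that a questionnaire carries information about sleep apnea, but they do not report its screening performance. Under the assumed odds ratio of 3, sensitivity could lie anywhere from 0.50 to 0.95 with specificity from 0.75 down to 0.14. A questionnaire with an AUC of about 0.63 would probably be significant at the planned size: about 92% power at 150 and 82% at 113, both at 50% prevalence.

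The odds ratio and the sensitivity and specificity values are illustrations, not figures from the article. The outcome is exploratory and the primary prevalence estimate is unaffected. The change is still worth making, because it bears directly on a purpose that the article states twice.

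**What to change.** In Statistical analysis, for STOP-BANG, Berlin and ESS separately:
- Report sensitivity, specificity and positive and negative predictive values at a cut-off fixed in advance, and the AUC of the score, all with 95% CIs.
- Use as reference the NightOwl AHI averaged over the four nights, at the protocol's own thresholds of 5 and 15, in all evaluable participants.
- State that NightOwl is itself an imperfect reference.
- Keep the logistic regression as a supplement, and say which terms enter it.
- Treat any comparison of the questionnaires with CRM as descriptive. After the first 20 participants, only those with AHI above 15 undergo CRM, so people at or below that level are represented only by the few among the first 20.

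The cost is a little extra analysis on data already planned, with no added visits or participants. The limit to accept is moderate precision, for example about 0.70 to 0.88 around an assumed sensitivity of 0.80 with 75 cases, and wider intervals for specificity if prevalence is well above 50%.
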